#### Concomitant medication

Medication use (e.g., bowel/bladder dysfunction, systemic hypertension, pain, spasticity, and antidepressant medications) is common after SCI and may confound the effects of our interventions. Because of participant safety and comfort, we will not limit prescribed medication use. We will require those receiving medication to maintain the dose 1 week before and during the intervention sessions, as we did in our previous study.^6,8^ The team physicians work with the study participant to ensure that medication dosing is stable before enrollment and during interventions. We log any change in medication for each participant throughout the study and assess for possible drug-tAIH interactions and changes in prescribed drug dosages at follow-ups. If participants must change their medications for safety, they can readily withdraw from the study at any time.

### Safety precautions

A designated research monitor (medical doctor) will oversee the safety of the research and report observations and findings to the IRB. This includes a review of unanticipated problems involving risks to participants or others and an independent report. To ensure participant safety, we implement the following precautions.

#### Protection against fall risk

Participants complete the walking training and assessments with a physical therapist to minimize fall risk. Participants also may use their least restrictive powerless assistive device. Participants will be asked about their fall history during the screening process, and any adverse events (falls) will be documented during the intervention.

#### Protection against fatigue risk

Assessment sessions may last up to 3 h. Only 60–90 min are dedicated to physical assessments, but this duration may be fatiguing to some. Most of the allotted time is devoted to subject preparation and instrumentation, done while the subject is sitting or lying down. During assessments, the evaluator and trained assistants monitor the participant for signs of fatigue and instability.

#### Protection against cardiopulmonary risk

During interventions, a team member monitors cardiopulmonary function to ensure safety and comfort. If excessive discomfort or pain is reported, the intervention ends. In case of medical issues that may arise during our interventions, such as symptoms of autonomic dysreflexia (AD), rapid change in HR or systolic BP (SBP), diaphoresis, severe headache, or dizziness, participants will be withdrawn from the experiment and provided skilled care from the research clinicians. The emergency medical team at the clinical sites are notified promptly. Return to the study requires medical clearance.

#### Protection against low oxygen risks

Moderate reduction in inspired oxygen can cause a lightheaded sensation, dizziness, reduced vision, and euphoria. The research team monitors SpO_2_, HR, and BP before, during, and after the breathing intervention to ensure that administered oxygen levels do not induce cardiopulmonary stress on participants. The breathing system automatically delivers normal room air to participants if their SpO_2_ level falls below 75%. Supplemental oxygen will be available for participants if needed. If participants report signs of a lightheaded sensation, dizziness, reduced vision, and euphoria, the experiment will be stopped, administration of room air or supplemental oxygen will be provided, and a physical therapist and/or physician will reassess the participant.

#### Protection against electrical shock

Risk of electrical shock is extremely low, and the SCONE device is limited to non-injurious current and voltage levels. The electrical stimulation device is routinely checked and constantly monitored for defects. Electrodes are checked before each session to maintain quality assurance. The emergency medical teams at the trial sites will be notified promptly if any electrical shocks occur.

#### Protection against skin irritation

Some subjects are sensitive to the hydrogel electrodes or adhesive used in medical-grade tape. This can result in temporary redness or itchiness in areas where tape has contacted the skin. We will ask subjects if they have known tape or adhesive sensitivity before the experiment begins. We use hypoallergenic medical-grade tapes and adhesives commonly used in hospitals.

#### Protection of confidential information

For participant confidentiality, all data will be coded and unrelated to identifiable information. Participants' names will only appear on the research consent form and not on any data sheets or files kept in the laboratory. Names or other information that could be used to identify persons will not appear when the study results are presented or published. However, video files will be created to serve as a visual record of the experiment, and they cannot be changed to disguise the participant's appearance. All research records, including video records, will be kept on computers accessible only to study staff or in locked archives.

Only study investigators, the investigator's staff, site IRBs, and the sponsor's Office of Human Research Oversight will have the authority to review the study records; they must maintain the confidentiality of each participant's identity. Records of ongoing participation in this study remain confidential and on Health Insurance Portability and Accountability Act–compliant computer systems or in a secure file cabinet in the site research offices. All research materials remain confidential until the study is completed, at which point all subject-sensitive research material will be destroyed. Results of this study may be used for publications or presentations at scientific meetings; if individual results are discussed, the participant's identity will be protected using a study identification number rather than identifying information.

### Outcome measures

We provide a summary of primary and secondary outcome measures in Table 2.

**Table 2. tb2:** Frequency of Clinical Assessments and Outcome Measurements

Measurement	Data collected	Time collected
Functional assessments		
Demographics	Age, sex, ethnicity, race, education	S
Medical history	SCI characteristics, medical records	S
Sleep quality^26^	Apnea-hypopnea rate	S
Medications	Name, dose, duration, and purpose	S, B, T, F
10-Meter Walk Test^71^	Time (s)	B, I, T, F
6-Minute Walk Test^72^	Distance (m)	B, T, F
Timed Up and Go Test^73^	Time (s)	B, T, F
WISCI II^74^	Scalar score (0–20)	B, T, F
SCI-FAI^41^	Scalar score (0–39)	B, T, F
Physiological assessments		
ISNCSCI exam^69,a^	SCI classification grade (A–E)	S
LEMS^42^	Scalar score (0–50)	B, T, F
SCATS^75^	Scalar score (0–18)	B, T, F
NPRS^43,44^	Scalar score (0–10)	B, T, F
NBDS^54^	Scalar score (0–47)	B, T, F
NBSS^55^	Scalar score (0–78)	B, T, F
Cardiovascular measures	Blood pressure, heart rate, SpO_2_, respiratory rate	B, I, T, F
Neurocognitive assessments		
MMSE^25^	Memory score (0–30)	S
CVLT3^49^	Total recall index score (40–160)	T
O-TMT^50^	Duration (s)	T

S = screening day; B = baseline; T = testing session; F = follow-up (1, 4, and 8 weeks); I = intervention day.

^a^
If no current/recent record of ISNCSCI exam is available.

CVLT3, California Verbal Learning Test, Third Edition; ISNCSCI, International Standards for Neurological Classification of Spinal Cord Injury; LEMS, lower extremity motor score; MMSE, Mini-Mental State Examination; NBDS, Neurogenic Bowel Dysfunction Score; NBSS, Neurogenic Bladder Symptom Score; NPRS, Numeric Pain Rating Scale; O-TMT, Oral Trail Making Test; SCATS, SCI Assessment Tool for Spastic Reflexes; SCI, spinal cord injury; SCI-FAI, SCI Functional Ambulation Inventory; WISCI, Walking Index for Spinal Cord Injury.

#### Gait

Overground walking ability is quantified by three primary measures: 10MWT (walking speed); TUG test (walking initiation and balance); and a 6MWT (walking endurance). These tests capture functional ambulation, exhibit high reliability and construct validity, and have precedence for quantifying and distinguishing degrees of functional ambulatory recovery post-SCI.^37–39^ Our previous study in persons with chronic SCI showed these tests to be more sensitive to changes in walking function and functional ambulation compared to American Spinal Injury Association Impairment Scale (AIS) grade or categorical ambulation metrics.^6,8^ During all walking assessments, we allow participants to use their least restrictive hand-held assistive device of choice.

Participants carry out two trials each for the 10MWT and TUG (at their fastest but comfortable and safe speed); the average speed will be used. A minimum of a 1-min rest between tests will be provided. Participants will perform the 6MWT only once at a walking speed sustainable for 6 min. The participant's walking distance at the 2- and 6-min mark will be recorded. We also record secondary outcome measures of walking function that include the Walking Index for Spinal Cord Injury (WISCI) II^40^ and SCI Functional Ambulation Index (SCI-FAI).^41^ To quantify strength, the AIS lower extremity motor scores (LEMSs) will be used.^42^

To quantify maladaptive changes that may occur subsequent to the combinatorial interventions, we measure pain, spasticity, systemic hypertension, AD, and cognitive ability during our assessments.

#### Pain severity

Pain severity is assessed using the 11-point Numeric Pain Rating Scale (NPRS) of 0 (no pain) to 10 (extreme pain). The NPRS has shown high test-retest reliability and interpretability as well as good content and construct validity for persons with SCI.^43,44^

#### Spasticity

Spasticity is assessed using rhe Spinal Cord Assessment Tool for Spastic Reflexes (SCATS)^45^; three subscales will be used to quantify spasticity in lower extremity clonus, flexor, and extensor spasticity.

#### Blood pressure

We will define a systemic hypertensive event as a systolic pressure exceeding 140 mm Hg and/or diastolic pressure exceeding 90 mm Hg.^46^ For each participant, we specifically record the hypertension incident rate, that is, the number of hypertensive events divided by units of person-measures (the total number of BP measurements), which accounts for the total number of chances for detecting a hypertensive event and for measurements not made because of dropout or a disqualifying adverse event.^47^

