### Study recruitment and enrollment

We established an interprofessional recruitment team at Spaulding Rehabilitation Hospital and Shirley Ryan AbilityLab. The recruitment team comprises the site principal investigators, clinical trial coordinators, research assistants, post-doctoral research fellows, onsite physicians, and research physical therapists. Our study recruitment process includes reviews of site-specific hospital patient registries, announcements through clinical research networks (e.g., Spinal Cord Injury Model Systems), clinicaltrials.gov, outreach to local outpatient rehabilitation centers, and media postings on relevant websites. Our team clinicians will also contact patients with SCI diagnoses admitted to our clinical sites that will likely meet the study criteria once they reach the chronic stage of injury. The study personnel contact potential participants using IRB-approved scripts to avoid bias or coercion during recruitment. Study participants must meet the study inclusion and exclusion criteria detailed in Table 1. These criteria align with the International Campaign for Cures of Spinal Cord Injury Paralysis recommendations^24^ and account for ethical considerations, safety, and potential confounds during participant recruitment.

**Table 1. tb1:** Study Eligibility Criteria

Inclusion criteria
• 18–70 years of age
• Medically stable with medical clearance from study physician to participate
• Incomplete SCI at and between levels C_2_ and L_2_ with at least some sensory or motor function preserved below the neurological level to ensure phrenic and cauda equina sparing
• Non-progressive etiology of SCI
• ISNCSCI Impairment Scale,^69^ Grade C–D
• Ambulatory, able to walk 10 meters without support from another person
• Chronic injury (≥12 months post-injury)^a^
Exclusion criteria
• Severe concurrent illness or pain^b^
• Less than a score of 24 on the MMSE^c^
• Severe recurrent autonomic dysreflexia per assessment by the study physicians
• History of severe cardiovascular/pulmonary complications, including hypertension (systolic blood pressure >150 mm Hg)
• Pregnancy^d^
• Botulinum toxin injections in lower extremity muscles within the last 6 months
• History of tendon or nerve transfer surgery in the lower extremity
• Untreated severe sleep-disordered breathing^e^
• Active implanted devices (e.g., intrathecal baclofen pump)
• Receiving electrical stimulation therapy

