• tSTIM-induced involuntary motor threshold is >200 mA (exceeding SCONE's current limit).

^a^
Chronic SCI to avoid the potential for spontaneous neurological plasticity and recovery.^16,70^

^b^
Illness including unhealed decubiti, severe neuropathic or chronic pain syndrome, severe infection (e.g., urinary tract), hypertension, cardiovascular disease, pulmonary disease, severe osteoporosis, active heterotopic ossification in the lower extremities, and severe systemic inflammation.

^c^
MMSE^25^ cutoff to avoid participants with cognitive impairment.

^d^
Pregnancy is an exclusion criterion because of unknown effects of tAIH or tSTIM on a fetus; persons of childbearing potential will not otherwise be excluded.

^e^
Severe sleep-disordered breathing (>30 apneas or hypopneas per hour).^26^

ISNCSCI, International Standards for Neurological Classification of Spinal Cord Injury; MMSE, Mini-Mental State Examination; SCI, spinal cord injury; tAIH, therapeutic intermittent hypoxia; tSTIM, transcutaneous spinal stimulation;

Potential participants undergo a medical screen by the study physicians and a physical/mental evaluation by the clinical research team. Eligible persons are informed of the study procedures and potential risks and sign the IRB-approved informed consent form before participation. The screening consists of a medical record review, assessment of the participant's ability to walk 10 m without human assistance, confirmation that their lower extremity involuntary motor threshold is <200 mA, and Mini-Mental State Examination (MMSE) score ≥24.^25^ We also screen for sleep-disordered breathing using a portable sleep monitor (Nox A1s PSG System; Nox Medical, Suwanee, GA or ApneaLink; ResMed Inc., San Diego, CA) at home for 1 night.^26^ After the screening, we deidentify study participants with a unique alpha-numeric identifier and associate this code with study-related documentation. This study received approval from the MGB IRB (#2022P002036) and the Department of Defense Office of Human Research Oversight in January 2023, and the first study participant enrolled in March 2023.

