#### Walking practice

Participants receive eight 45-min WALK sessions over 2 consecutive weeks. The WALK sessions consist of intensive walking-related functional tasks using a skill-based training approach.^6^ The training includes activities related to walking speed (10MWT), initiation and balance (TUG), and walking endurance (6MWT). Recent studies found that skill-based walking practice is more consistent with community walking, providing meaningful gains in walking function after neurological injury.^28–31^ Walking practice emphasizes learning sensorimotor skills for community walking, including walking speed, endurance, stepping balance, and initiation.^30^ Participants may rest up to 15 min during the practice sessions. During the WALK sessions, the physical therapist trainer will provide physical assistance as needed for safety. Step count, peripheral blood oxygen saturation (SpO_2_), heart rate (HR), and blood pressure (BP) are measured at each session.

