#### Autonomic dysreflexia incidence rate

AD incidence rate is the number of AD events divided by the total person-time (number of study days completed by each participant) to account for the total number of chances for detecting AD for days not measured because of dropout or a disqualifying adverse event.^47^ An AD event will constitute a participant having a SBP increase from baseline of 20 mm Hg not associated with exercise or SBP >150 mm Hg with complaints of headache, diaphoresis, and/or blurred vision and will be diagnosed by our study team clinicians (physicians and physical therapists).

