### Adverse event reporting

The research team will record adverse events related to each participant from the time of enrollment to the last follow-up assessment visit, which include: 1) unintentional loss of balance (i.e., fall to the ground); 2) change in systolic pressure to >140 mm Hg and/or diastolic pressure exceeding >90 mm Hg^46,60^; 3) AD with SBP >150 or >20 mm Hg from baseline with complaints of headache, diaphoresis, and/or blurred vision; 4) musculoskeletal injury during/after walking training (i.e., sprain, fracture, etc.); 5) symptoms such as pain, soreness, numbness, or signs of injury (inflammation, blisters, etc.) during or immediately after training or on returning home; 6) hospitalization for any cause; and 7) death attributable to any cause. Serious and/or unexpected adverse events will be immediately reported to the MGB IRB.

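### The hypertension rate for Aim 3 has no baseline reference and no start point, so entry pressure and pre-assignment readings can count as events, diluting a true effect and letting chance imbalance move the relative risk.

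*Protocol article*

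**What the plan says.** **Event and rate.** The Blood pressure section defines the event by absolute limits: "We will define a systemic hypertensive event as a systolic pressure exceeding 140 mm Hg and/or diastolic pressure exceeding 90 mm Hg". The rate recorded for each participant is "the number of hypertensive events divided by units of person-measures (the total number of BP measurements". Neither statement refers to the participant's own earlier pressure, to when counting starts, or to the conditions of measurement.

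**Entry.** Table 1 excludes "History of severe cardiovascular/pulmonary complications, including hypertension (systolic blood pressure >150 mm Hg"; no diastolic limit is given. Footnote b to that table, which lists examples of severe concurrent illness, includes hypertension with no cut-off: "severe infection (e.g., urinary tract), hypertension, cardiovascular disease, pulmonary disease". The Concomitant medication section expects treated hypertension among participants: "Medication use (e.g., bowel/bladder dysfunction, systemic hypertension, pain, spasticity, and antidepressant medications) is common after SCI".

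**When pressure is read.** Table 2 schedules cardiovascular measures at baseline, intervention days, test sessions and follow-ups. The Walking practice section says that "heart rate (HR), and blood pressure (BP) are measured at each session". The Randomization section has participants assigned to a group in the order in which they complete walking practice, so baseline and the eight practice sessions precede assignment.

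**Neighbouring definitions.** The first autonomic dysreflexia criterion is a systolic rise of 20 mm Hg from baseline that is "not associated with exercise". The Adverse event reporting section uses the same 140/90 limits, worded as a "change in systolic pressure to >140 mm Hg and/or diastolic pressure exceeding >90 mm Hg".

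**Analysis.** Under Hypothesis 3, incidence rates are compared between interventions by relative risk with a 95% confidence interval. The prediction is that the risks do not differ.

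**The concern.** Hypothesis 3 asks whether the combination induces maladaptive change, including systemic hypertension. A count of all readings above a fixed limit measures prevalence. It mixes events that arise under treatment with pressure that was already high at entry, and with readings taken before anyone had a group.

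Two things are at stake. Events unrelated to treatment add equally, in expectation, to both sides of the ratio and pull it toward 1, which is the result that the protocol predicts. And with 16 to 20 people per arm, where a few participants with high entry pressure happen to fall can shift the relative risk with no treatment effect at all. The autonomic dysreflexia definition already carries a baseline reference and an exercise qualifier for its first criterion; the hypertension definition carries neither.

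**Working it through.** The protocol gives no expected hypertension rate and no power for this outcome, so there is no figure to reproduce. All blood-pressure rates below are assumptions; group sizes (20 enrolled, 16 completing) come from the Randomization and Sample size sections.

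**1. Can a participant meet the definition at entry?** The event begins above 140 systolic and the numeric exclusion begins above 150, so that exclusion leaves 141 to 150 open. Footnote b could be read as closing it, but it gives no cut-off, stands under severe illness, and sits beside a medication section that expects treated hypertension. Entry at 141 to 150 is therefore possible on the text, not certain.

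**2. How often would such a person score an event?** Assume normally distributed readings with a within-person SD of 8 to 12 mm Hg. The probability of a reading above 140 is 1 − Φ((140 − mean)/SD).
- Mean 145: 73% (SD 8), 69% (SD 10), 66% (SD 12).
- Mean 150: 89%, 84%, 80%.

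A range of 70% to 100% of readings therefore runs from a typical to an extreme case.

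**3. One such participant in one arm, none in the comparator, no treatment effect.** With equal numbers of readings per person, background rate p and that participant's rate f, RR = ((n − 1)p + f)/(np).
- p = 5%, f = 100%: n = 20, (0.95 + 1)/1.00 = 1.95; n = 16, (0.75 + 1)/0.80 = 2.19.
- p = 5%, f = 70%: n = 20, (0.95 + 0.70)/1.00 = 1.65; n = 16, (0.75 + 0.70)/0.80 = 1.81.
- p = 2%, f = 100%: 1.38/0.40 = 3.45; 1.30/0.32 = 4.06.
- p = 10%, f = 100%: 2.90/2.00 = 1.45; 2.50/1.60 = 1.56.

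If two groups were pooled on one side (tAIH against placebo, or stimulation against sham) and the person fell on the pooled side, the 5% case would be milder. At f = 100%: n = 40, (1.95 + 1)/2.00 = 1.48; n = 32, (1.55 + 1)/1.60 = 1.59.

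**4. Dilution by unrelated readings.** Let b be the share of readings above the limit for reasons other than treatment, and let treatment double new events from 5% to 10%. RR = (b + (1 − b) × 0.10)/(b + (1 − b) × 0.05).
- b = 0: 2.00
- b = 5%: 0.145/0.0975 = 1.49
- b = 10%: 0.190/0.145 = 1.31
- b = 20%: 0.280/0.240 = 1.17
- b = 30%: 0.370/0.335 = 1.10

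**5. Dilution by pre-assignment readings.** If a share w of readings precedes assignment and runs at 5% in both arms, the same doubling shows as (0.05w + 0.10(1 − w))/0.05 = 2 − w. With one reading in each of the 16 intervention sessions, w = 8/16 and the RR is 1.50. If each treatment session adds three breathing-intervention readings (15 episodes, every fifth), w = 8/(8 + 32) = 0.20 and the RR is 1.80. Readings per session are an assumption, and baseline, test and follow-up readings are left out.

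**The case against.** Entry at 141 to 150 is not certain. Footnote b may bar it, a study physician must clear each participant, and taking antihypertensive drugs does not imply uncontrolled pressure. This stands, and is why the point says that a participant may meet the definition at entry. Counting pre-assignment readings does not depend on it.

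A reader might infer that the rate counts exercise as harm, or mostly reflects how hard people walked. The text does not support that. It says that pressure is measured at each session, not whether before, during or after walking, and a condensed article may leave such timing to the full protocol. What stands is that nothing in the definition sets such readings apart if they are taken.

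A reader might also infer bias against the combination arm. Allocation is random and all three groups do the same walking, so entry pressure and exercise balance in expectation. Only dilution and chance imbalance remain. The Study limitations section plans multivariable models for potential confounders and medication as a covariate, but it does not name entry blood pressure, so this helps only in part.

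Finally, the adverse-event wording, which speaks of a change to above the limit, can be read as requiring a new rise. The outcome definition does not carry that over, so the two need to be aligned.

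**Conclusion.** The point holds in this limited form. The definition can count entry status and pre-assignment readings in a comparison meant to show whether treatment induces hypertension. The effect is dilution toward a relative risk of 1 plus sensitivity to chance imbalance, not a systematic advantage to any arm.

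The illustrated sizes rest on assumed event rates, equal readings per person and, for the single-participant case, one such person in one arm and none in the comparator. That an eligible participant would score an event at almost every reading is an extreme case; 66% to 89% is the more plausible range under the assumed SDs. The protocol gives no data on how many participants enter above 140/90, so how large the problem will be in this trial cannot be stated. A change is worth making because the outcome carries part of the safety hypothesis and the remedy is cheap.

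**What to change.** For the between-group comparison:
- Count only readings taken after group assignment, with a denominator restricted in the same way.
- Reference events to the participant's own pre-treatment value (baseline or T0, both already scheduled), or adjust the rate for that value. Do not use the same session's pre-intervention reading: from the second treatment session on it is itself post-treatment, so a cumulative rise could be hidden.
- Report mean change from the pre-treatment value for all participants, including those who start above 140/90, and keep the follow-up readings.
- Tabulate separately any readings taken during or just after walking.
- Keep the absolute-threshold adverse-event log as it is.

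Reconcile Table 1, its footnote b and the Blood pressure, Autonomic dysreflexia incidence rate and Adverse event reporting sections on entry limit, baseline reference and measurement condition. Which limits apply is for the sponsor to decide.

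The cost is fewer counted events and slightly more analysis. The pre-treatment values are already in the assessment schedule.
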